### Food diary protocol

The weighed food diary will commence on the participants day of surgery (day zero) and will conclude at post-operative day three inclusive. The weighed food diary will consist of the researcher using an electronic digital kitchen scale with a weight graduation of 1 g (AccuWeight 201, maximum weight 5 kg) to weigh all items served to the participant before and after their mealtime. The researcher will not serve any food directly, with plates or bowls placed directly on the digital scale and recorded by the researcher. Should a food be packaged with a specified weight – for example a yoghurt, said weight on the packaging will be recorded. Fluid intake will be recorded according to each mealtime (e.g. a cup of tea or fruit juice) and the researcher will liaise with the ward staff to log how many jugs of water the participant has consumed daily, and if this has been accompanied with other items such as cordial. A baseline measurement of water jugs, cups and beakers will be taken prior to the study commencing.

The researcher will not be present nor disrupt the participant during their meal, and after their food tray has been retrieved, the researcher will weigh the plate if it is a complete meal (e.g. lasagne), or, if it is a multiple item meal (e.g. meat, potatoes and vegetables), the researcher will weigh the leftover components individually to ensure the validity of the weighed food method and to achieve the highest degree of accuracy possible. After mealtime has concluded, the researcher will briefly ask the participant if they have had any snacks between their meals. Any observed assistance with meals (such as a family member) will be confirmed with ward staff. Additionally, as part of the specific NOF pathway in place, all hip fracture patients regardless of MUST screening assessment are required to consume two oral nutritional supplements (Nutricia™ Fortisip Compact or Fortisip Compact Protein) daily. The researcher will liaise with the ward staff regarding consumption and additionally will record the amount consumed. Data will also be collected regarding the times of meals and the ratio of staff to patients on the ward during each mealtime.

The researcher will liaise daily with the participant's named nurse regarding complications that may develop post-operatively during the study period, such as delirium, pressure ulcers, infection and venous thromboembolism.

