### Adverse events

Should a participant experience an adverse event during the study, such as a stroke, myocardial infarction, major haemorrhage requiring a blood transfusion, the participant will be removed from the study, which was agreed after consultation with the study site research department. If a participant is removed from the study due to an adverse event, any data collected up until that point will be kept in the study and anonymous and an adverse events record made. The participants’ end point in the study will be when LOS and discharge destination data is obtained by the researcher.

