### Data storage and analysis

Participant identifiable data (name, date of birth and hospital number) will be used to create a unique identifier that will ensure the correct food diary data is recorded against the correct patient, when accounting for a participant's potential movement between rooms during their ward stay. Once the participant's LOS and discharge destination data has been obtained, the participant's data will be anonymised and assigned a unique reference number. All participant data will be recorded and held within the trust site to maintain confidentiality and the transfer of patient information once assigned an identifier will be from the research department to the researcher's secure email.

Baseline nutritional requirements for REE, total energy expenditure (TEE), protein, carbohydrates and fat nutritional requirements per day will be calculated according to the specific guideline formula (Todorovic and Mafrici, 2018). In the instance where BMI is outside of the range 18.5 to 30 kg/m^2^, calculation adjustments will be made as per the guideline recommendations (Todorovic and Mafrici, 2018). Regarding physical activity and diet-induced thermogenesis (PAL), a combined factor range of 1.0 to 1.10 will be used, which the guidelines state is a ‘post-surgery factor’ (Todorovic and Mafrici, 2018). In cases where there is a range specified, calculations of nutritional requirements will be made at both the lower and higher scale. Demographic variables will be presented in descriptive summaries such as mean ± SD and median for continuous variables and percentages for categorical variables. For statistical analysis we will present descriptive statistics for REE met per day and to make inferences, we will take an average of the proportion of REE intake of the total food diary.

Multiple regression analysis will be used to explore if REE is a predictor of LOS, with post-operative complications and medical history used as confounders along with those who have capacity or not. Due to a small sample size, we acknowledge that caution should be taken with secondary subgroup analysis. In addition, where REE is met or exceeded, participants food diaries will be scrutinised to explore if this is attributed to a specific category of food (e.g. a high-fat dessert item) and where REE is not met, food diaries will be scrutinised to explore if this is related to complications reported.

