### Ethics and dissemination

Ethical approval and permissions for this study were sought from:
NHS Ethics – approval was granted by the Health Research Authority (REC reference: 24/NE/0034)This study is registered at ClinicalTrials.gov (NCT06451679)The study will be conducted in accordance with the principles of the Health Research Authority (HRA) Good Clinical Practice (NHS HRA, 2020) and adhere to appropriate legislation regarding the protection of data for participants in the study (NHS HRA, 2021).

Written informed consent will be obtained from participants that have been assessed by a medical doctor as having capacity on admission following a discussion of the study between the participant and the researcher. Should a participant lack capacity, the researcher will approach the participant for inclusion in the study after a discussion with medical staff (the Consultee) regarding suitability. Ward medical staff will be given a briefing before the study commences and issued with a Consultee Information Sheet (CIS). If the participant is suitable, the Consultee will introduce the researcher to a family member/friend whereby with an introduction of the study, their opinion will be sought as to whether they believe their family member or friend that has sustained a hip fracture would be likely to consent to taking part in the study if they had capacity. If they agree, the Consultee will complete a specific ‘Consultee Form for Participants Lacking Capacity’. All participants will be informed that they can withdraw from the study at any time with no reason required, and, should a participant lack capacity initially and subsequently regain capacity, they will be informed immediately of the study and will be able to remain in the study, withdraw from study and withdraw their data, or withdraw from the study and allow the researcher to keep their data up until that point.

Results from the observation study will be reported using the Strengthening the Reporting of Observational Studies in Epidemiology (STROBE) guidelines (Von Elm et al., 2007) and disseminated at relevant scientific conferences and by publication of peer-reviewed manuscripts.

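### Partial diaries are kept and inference uses one raw average per participant, so diary length can be confounded with length of stay and complications in the exploratory associations

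*Protocol article*

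**What the plan says.** All four statements are in the protocol article.

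- **Window** (Food diary protocol): the diary "will commence on the participants day of surgery (day zero) and will conclude at post-operative day three inclusive", which is four days.
- **Removal** (Adverse events): after a stroke, a myocardial infarction or "major haemorrhage requiring a blood transfusion, the participant will be removed from the study". The partial record is retained: "any data collected up until that point will be kept in the study and anonymous".
- **Withdrawal** (Ethics and dissemination): a participant who regains capacity has three options, one of which is to "withdraw from the study and allow the researcher to keep their data up until that point".
- **Analysis** (Data storage and analysis): "we will present descriptive statistics for REE met per day", but to make inferences "we will take an average of the proportion of REE intake of the total food diary". Multiple regression then examines REE as a predictor of length of stay (LOS), adjusting for complications, medical history and capacity. I take the predictor to be this average. The Dietary intake section also makes intake a predictor of complications.

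The analysis section does not separate a one-day diary from a four-day diary.

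**The concern.** The average is the same quantity for every participant only if everyone contributes the same days. Early leaving does not remove days at random: it always keeps the day of surgery and always loses the end of the window. The Introduction mentions preoperative fasting, and the Hypothesis section attributes reduced intake to trauma, anaesthesia and surgery. Low intake on day 0 with some recovery afterwards is therefore a reasonable expectation, though the article gives no daily figures.

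If intake does rise, a participant with a short diary gets a lower score than one with a complete diary who ate in exactly the same way. The stated triggers for removal are serious events that may well go with longer stay and with complications. The artefact would then point the same way as the second hypothesis, that reduced intake worsens LOS and complications. At stake is the reading of those two exploratory associations in a sample of 30.

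**Working it through.** The article states no figure for this point that could be reproduced. Its inputs are the four-day window, the retention of partial diaries, the single average and the sample of 30. The daily profiles, SDs, LOS values and numbers leaving early below are all assumptions.

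**Step 1: weight of the day of surgery.** Averaged over observed days, day 0 has weight 1/4 in a complete diary, 1/3 when leaving after day 2, 1/2 after day 1 and 1 after day 0. These are different quantities placed in one regression column.

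**Step 2: gap for one participant leaving after day 1.** Let p0 to p3 be the percentage of REE met on days 0 to 3. Then

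gap = (p0+p1+p2+p3)/4 − (p0+p1)/2 = [(p2+p3) − (p0+p1)]/4.

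| Assumed profile (% of REE) | Complete | Days 0–1 only | Gap |
|---|---|---|---|
| Steep rise 20/40/50/60 | 170/4 = 42.5 | 60/2 = 30.0 | 12.5 |
| Mild rise 35/42/46/47 | 170/4 = 42.5 | 77/2 = 38.5 | 4.0 |
| Flat 42.5 on each day | 42.5 | 42.5 | 0 |

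Leaving after day 0 gives 20.0, 35.0 and 42.5 respectively. Leaving after day 2 gives 36.7, 41.0 and 42.5.

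Dropping day 0 for everyone would not remove the problem. Days 1–3 against day 1 alone gives 50 versus 40 (steep) and 45 versus 42 (mild).

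**Step 3: cohort mean.** With m of 30 leaving after day 1, the mean is [(30 − m) × 42.5 + m × short average]/30.

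- Steep, m = 3: (27 × 42.5 + 3 × 30.0)/30 = 41.25. With m = 5: 40.4.
- Mild, m = 3: (27 × 42.5 + 3 × 38.5)/30 = 42.1. With m = 5: 41.8.

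The mean moves by about 2 points at most.

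**Step 4: association with LOS when none exists.** The simulation had 30 participants, between- and within-participant SDs of 12 points, and log-normal LOS with median 14 days and log-SD 0.5. Three or five participants left after day 0, 1 or 2 with equal probability and stayed 10 days longer. The test was an unadjusted Pearson correlation at 5%, with 4,000 runs per scenario and averages over observed days.

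| Profile | False positives, 3 leavers | False positives, 5 leavers | Mean correlation (3; 5 leavers) |
|---|---|---|---|
| Steep | 8.4% | 12.7% | −0.10; −0.15 |
| Mild | 5.0% | 6.0% | −0.04; −0.05 |
| Flat | 4.5% | 5.4% | 0.00; 0.00 |

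With no truncation the rate was 4.6% to 5.7%. Adjustment for complications was not modelled.

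**The case against.** A journal article need not give every missing-data rule, and a fuller document may define how incomplete diaries are handled. That is fair for the detail. But the article itself fixes both that partial diaries are kept and that inference rests on one raw average, and the non-comparability follows from those two choices together.

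Four stronger readings are tempting, and the article does not support them.

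- *Unobserved days count as zero.* A reader might infer division by the four planned days. That would always lower the score: even the flat profile would fall from 42.5 to 85/4 = 21.25. The denominator is not stated, and nothing says that unrecorded days are zeros.
- *A short diary is always scored lower.* Over observed days this holds only if intake rises. The gap is nil for a flat profile.
- *Early discharge adds short diaries with short stays.* The article does not describe discharge or transfer before day three, only movement between rooms.
- *The share failing to meet REE is inflated.* Under these profiles, complete and short diaries both fall far below 100%, so the classification does not change. REE met is also described day by day, which largely protects the primary aim.

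Two further points limit the LOS result. It is unclear whether LOS is obtained for removed participants; if it is not, they drop out of that model. Adjustment for complications may also absorb part of the effect. The named complications (delirium, infection, pressure ulcers, venous thromboembolism) do not include the removal events, although the list in the Food diary protocol section is given as examples. Adjustment cannot help where complications are the outcome.

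**Conclusion.** The point holds in a limited form. Following the stated rules puts averages over different days into one predictor, and the reason for a short diary can be related to the outcomes. For a participant leaving after day 1, the artefact is 0 to 12.5 points of REE, depending on a day trend that the article does not quantify. With three to five such participants who also stay longer, the false-positive rate for intake versus LOS stays near 5% under a flat or mild profile and reaches about 8% to 13% under a steep one. These figures rest on assumed profiles, SDs, LOS values and numbers leaving, and on an unadjusted test. The consequence is confined mainly to the exploratory LOS and complication associations.

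**What to change.** For inference, replace the raw average with a day-standardised measure:

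- Model the patient-day proportion of REE met (at most 30 × 4 = 120 patient-days), with diary day as a categorical fixed effect and participant as a random effect.
- Use all observed days, and state that unobserved days are missing and never zero.
- Use the participant's day-adjusted level from this model in the LOS and complication analyses.
- Repeat both analyses in participants with complete diaries as a sensitivity analysis.

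The per-day descriptive summaries can stay as they are.

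The cost is a few lines of analysis text and one simple model, with no extra data collection. The day-adjusted level is slightly less intuitive than a raw average. The model also assumes that unobserved days are missing at random given the observed days. That assumption is strained when participants leave because they are ill, and should be stated as a limitation. The wording should be fixed before the data are examined.

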### Study sample

The study aims to recruit 30 older adult hip fracture patients admitted to an orthopaedic trauma ward for surgical repair of a hip fracture. A district general sized hospital was chosen as opposed to the scale of a trauma/transplant centre hospital to confer greater generalisability to the population in England with the findings from this study. A sample size of 30 was agreed by the research team based on the admissions data published by the NHFD for the specific study site and is reflective of a ‘typical’ average month of admissions to the hospital, according to 2021 and 2022 data. The decision to enrol 30 patients was primarily based on funding constraints, as there are currently no available funds to support a larger sample. This number was chosen to ensure we can gather detailed and meaningful data while adhering to our timeline and resources. The recruitment period will last for a continuous period of 4 weeks, and all eligible patients according to the inclusion and exclusion criteria will be invited into the study via the gatekeeper as they are admitted to the hospital ward. The standard diagnosis for a hip fracture is an x-ray on admission to the accident and emergency department, following which, the participant's care adheres to a specific ‘neck of femur (NOF) fracture pathway’ which is already in place at the study site.

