### Enrolment procedure

With agreement, the researcher will discuss the study with the participant and family or carers if present and provide the participant with a patient information sheet (PIS) and consent form to read in full. After 1 hour, the researcher will return and obtain informed consent. The lead researcher for this study is a current registered healthcare professional with the Health and Care Professions Council in the UK and has training and experience of obtaining written informed consent. With the participants consent, the researcher, working with the specialist nurse will obtain data from the participant's medical records pertaining to outcome measures (Table 1).

**Table 1. table1-02601060241307768:** Outcome measures.

Variable	Instrument/scale
Age	Age will be measured in years based on the date of birth obtained from medical records.
Sex	As recorded in medical records.
Ethnicity	As recorded in medical records.
Original domicile	Defined as own home/care home/sheltered accommodation, according to medical records.
Mobility status prior to admission	Defined as independent/independent with 1 stick/independent with 2 sticks/independent with frame/wheelchair.
Nutritional screening	Screening assessment according to the Malnutrition Universal Screening Tool (0, 1 or 2).
BMI	Calculated by ward staff; where not possible, MUAC score.
REE	Calculated according to guidance (Todorovic and Mafrici, 2018)
Smoking status	Confirmed on admission; answered as yes or no.
Alcohol	Confirmed on admission; calculated as units per week.
Fracture type	Classified as intra-capsular or extra-capsular, confirmed on admission with an x-ray performed in the emergency department.
ASA Grade	Classified following anaesthetic pre-assessment by anaesthetist (1–5).
Acute length of stay	Measured from admission to discharge from the acute ward, in days.
Discharge location	Defined as original domicile/rehabilitation unit/care home.
Past medical history	Data will be obtained from medical records regarding cardiovascular, respiratory, diabetes, cognitive decline, arthritis and history of previous fractures.

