#### Dietary intake

We will analyse if dietary intake is sufficient to meet estimated REE requirements and explore the effect of dietary intake as a predictor of LOS and post-operative complications. Current guidelines will be used to calculate REE, and we will use a factor of 23 kcal/kg actual body weight per day for ‘surgical fixation of a hip fracture’ according to the supporting evidence-based recommendations specified in the guidelines (Todorovic and Mafrici, 2018). Using macronutrient data for hospital meals provided by the trust, consumption and waste per meal will be calculated according to energy (kJ/kcal), protein, carbohydrates, fats and fibre. For any snacks consumed or foods not listed by the hospital, Nutritics v6.00 software will be used for macronutrient data (Nutritics, 2024).

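### The length-of-stay regression names REE, a requirement, as its predictor where the rest of the plan points to intake, and it adjusts for complications that the plan elsewhere treats as outcomes of intake.

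*Protocol article*

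**What the plan says.** All places are in the protocol article.

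- **Model.** Data storage and analysis states: "Multiple regression analysis will be used to explore if REE is a predictor of LOS". It names post-operative complications, medical history and capacity as the adjusters.
- **REE.** Under Dietary intake: "we will use a factor of 23 kcal/kg actual body weight per day". Data storage and analysis adds that the calculation is adjusted when BMI lies outside 18.5 to 30 kg/m².
- **Other statements of the exposure.** The sentence immediately before the model says "to make inferences, we will take an average of the proportion of REE intake of the total food diary". Dietary intake says the study will "explore the effect of dietary intake as a predictor of LOS and post-operative complications". The secondary aim for LOS, under Research aims, is about post-operative dietary intake.
- **Adjuster items.** Table 1 lists medical history as "cardiovascular, respiratory, diabetes, cognitive decline, arthritis and history of previous fractures". Food diary protocol describes complications "such as delirium, pressure ulcers, infection and venous thromboembolism". Research aims names the same four.
- **Sample.** "The study aims to recruit 30 older adult hip fracture patients" (Study sample). The basis given is that "The decision to enrol 30 patients was primarily based on funding constraints", together with a typical month of admissions.
- **Caution about size.** Data storage and analysis limits its small-sample caution to secondary subgroup analysis. Strengths and limitations adds caution about generalising.

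**The concern.** There are two problems in one sentence.

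First, the exposure. REE is what a patient needs, not what the patient eats. Three candidate predictors can be read from the article (REE, intake in kcal, proportion of REE met), and they are different variables that can give different answers. An analyst who follows the model sentence to the letter would publish a result on LOS that says nothing about diet.

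Second, the adjusters. Complications are outcomes of intake in Research aims, Hypothesis and Dietary intake, but confounders in the model. If low intake leads to complications and complications lengthen stay, adjusting for them removes part of the effect the study wants to see. The adjuster list may also be long for 30 patients, and its form (separate items or composites) is not stated.

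**Working it through.** No calculation lies behind the 30 patients, so there is no stated figure to reproduce.

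**1. What the literal predictor contains.** Inside BMI 18.5 to 30, REE = 23 × weight, so its correlation with weight is 1 by construction. Illustration with assumed values: two patients of 65 kg both have REE = 23 × 65 = 1,495 kcal. If one takes in 650 kcal/day and the other 1,350, the literal predictor is identical for both. The proportions met are 650/1,495 = 0.43 and 1,350/1,495 = 0.90. Outside that BMI range REE is an adjusted figure, but it still contains no intake.

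**2. What the proportion contains.** Proportion met = intake / (23 × weight), so weight is in the denominator. In a simulation with assumed weight 65 (SD 13) kg and independent intake of mean 1,000 and SD 200 to 450 kcal/day, the proportion correlated 0.67 to 0.88 with intake and −0.70 to −0.42 with weight. The proportion is mainly an intake measure but not free of body size.

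**3. Number of slopes.** If each item enters separately (an assumption): 1 predictor + 4 complications + 6 history items + 1 capacity = 12. With one composite for complications and one for history: 1 + 1 + 1 + 1 = 4.

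**4. Consequences.** Patients per slope = n/k, residual df = n − k − 1, and expected R-squared when nothing is related = k/(n − 1).

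| n | slopes k | n/k | residual df | expected null R-squared |
|---|---|---|---|---|
| 30 | 12 | 2.5 | 17 | 12/29 = 0.41 |
| 30 | 4 | 7.5 | 25 | 4/29 = 0.14 |
| 25 | 12 | 2.1 | 12 | 12/24 = 0.50 |
| 20 | 12 | 1.7 | 7 | 12/19 = 0.63 |

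The rows below 30 are illustrative. The Adverse events section provides for removal of participants but gives no rate. With 12 slopes and n = 30, an observed R-squared of 0.50 adjusts to 1 − 0.50 × 29/17 = 0.15.

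**5. Power for the single slope.** This uses a noncentral F test with 1 and n − k − 1 df, noncentrality f² × n, assumed two-sided alpha 0.05 and n = 30. At f² = 0.15, power is 0.52 with 12 slopes and 0.53 with 4. At f² = 0.35 it is 0.86 and 0.88. This holds the partial effect fixed, so it leaves out any widening from correlated adjusters. On this measure the extra terms cost little power. The harm lies in unstable, sparse terms and a flattering R-squared.

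**6. Variable roles side by side.** Hypothesis expects reduced intake to worsen LOS and complications. Dietary intake makes complications an outcome of intake. Data storage and analysis makes them confounders. The Covariates section lists LOS, the outcome of this model, together with complications. The roles are not settled.

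**The case against.** The strongest reply is that REE is shorthand. The preceding sentence bases inference on the average proportion of REE taken in, and the aims and the Dietary intake section pair LOS with intake. That reply stands as a reading of intent. A reader might infer that the study will simply test body weight as a predictor of LOS, but the article does not support so firm a claim. What it supports is that the sentence defining the model names a different variable from the aim it serves.

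The count of 12 slopes is not the article's either. It names three groups of adjusters, the complications list is open-ended, and coding is commonly left to a fuller document. This also stands, so 12 must be read as the upper case and about 4 as the composite case. The null R-squared matters mainly if model fit is interpreted. The slope's confidence interval already reflects the residual df.

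A reader might also infer that age, ASA grade and prior mobility are the main confounders and have been wrongly left out. Table 1 collects them and the stated adjuster set omits them, but nothing in the article ranks them. Nor does it give prevalences from which to say how often a 12-slope model would fail to be estimable.

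On complications there is a partial defence. Hypothesis also links reduced intake with delirium without fixing a direction, and the analysis section will look at whether unmet REE relates to reported complications. A complication that comes before poor intake could confound. But complications are recorded during the diary days, so the order is not established, and the plan cannot treat them as outcome and confounder without saying which applies where.

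Finally, this is a secondary, exploratory analysis and the primary aim is untouched. That limits the consequence, but an exploratory model still needs the right exposure.

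**Conclusion.** The point holds in this form: the exposure in the LOS model is contradictory, and complications are given two incompatible roles. Both follow from the text without any assumption. Taken literally, the model omits intake and cannot answer the intake-LOS aim.

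The size of the adjuster problem depends on coding. At n = 30 it ranges from 4 slopes (7.5 patients each, null R-squared 0.14) to 12 slopes (2.5 patients each, null R-squared 0.41), the latter only if every item enters separately. The correlations of the proportion with weight and the power figures rest on the assumed inputs shown. The exposure should be settled before analysis, because the choice among three candidate predictors should not be made after the results are seen.

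**What to change.** Rewrite the model sentence as follows.

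- **Predictor:** the mean proportion of REE met over the food diary (day 0 to day 3). Include body weight in the model, or add a sensitivity analysis with intake in kcal, because weight is in the ratio's denominator.
- **Adjusters:** a small prespecified set of baseline variables already collected, for example age, ASA grade or prior mobility, and capacity, with a single comorbidity count if needed. The choice among them is a judgement for the study team.
- **Complications:** leave them out of the main LOS model and analyse them as outcomes of intake, as the aims state.
- **Reporting:** the slope with its 95% CI, labelled exploratory.

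With weight in the model and one term per adjuster, the example has 5 slopes (30/5 = 6 patients per slope, 24 residual df, null R-squared 5/29 = 0.17), or 6 with the comorbidity count (5 per slope, 23 df, 6/29 = 0.21). Adding age, ASA grade and mobility to all 11 separate adjusters would instead give 15 slopes, 14 residual df and 15/29 = 0.52, so new terms must replace old ones.

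The cost is one rewritten sentence and no new data. Individual comorbidities are no longer adjusted for one by one. Including weight may widen the interval: at the simulated correlations of −0.42 to −0.70, the factor 1/√(1 − r²) is about 1.10 to 1.40. The case for the change is a defined exposure and a defensible adjuster set, not a promised gain in precision.
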